### Data management and analysis

2.5

The analysis plan for quantitative data includes a description of outcomes. The normality of continuous variable distributions will be assessed using the Shapiro–Wilk test. Depending on the results, data will be presented as either mean and standard deviation (for normally distributed variables) or median and inter-quartile range (for non-normally distributed variables). Categorical variables will be described using absolute frequencies and percentages. Comparisons between outcomes and exposures will be performed as follows: Chi-square tests for categorical variables; *t*-tests or one-way ANOVA for comparisons involving normally distributed continuous variables across groups; and non-parametric tests such as the Wilcoxon rank-sum test or Kruskal–Wallis test for non-normally distributed continuous variables. Correlations between continuous variables will be assessed using either Pearson’s or Spearman’s correlation coefficients, depending on the distribution. Although the primary aim of the study is assessing the intervention feasibility, in addition to *p*-values, effect sizes will be calculated and reported to quantify the magnitude of observed differences and associations, even if they are not statistically significant. In addition, in the absence of a control group, effect sizes for within-subject changes (pre–post) will be calculated (e.g., Cohen’s *d* for paired samples) to quantify the magnitude of change over time. These estimates will support the interpretation of the practical relevance of the findings, although causal inferences cannot be established.

Temporal comparisons (T0 vs. T2) will be conducted using paired-sample *t*-tests. If significant differences are identified in univariate analyses, multivariate models will be considered. Results will be reported as coefficients with standard errors (for continuous outcomes) or odds ratios with 95% confidence intervals (for binary outcomes), as appropriate. Model fit will be evaluated using *R*-squared or pseudo *R*-squared values.

In accordance with the intention-to-treat (ITT) principle, participants who withdraw from the study will not be replaced. Missing data in co-variates will be handled using multiple imputations via chained equations. All statistical analyses will be conducted by a statistician blinded to group allocation. A significance level of *p* < 0.05 will be used throughout. Analyses will be performed using SPSS for Windows, version 24.0 (SPSS Inc., Chicago, IL, USA).

Qualitative data are analyzed thematically following Braun and Clarke’s (2006) approach. Two independent researchers will analyze the textual data, with a third reviewer verifying the results to ensure reliability (Golafshani, 2003; Lincoln and Guba, 1985; Shenton, 2004). Observational notes, reports (and, when shared, also the diaries written by caregivers) will be compiled into narratives and then summarized across countries (Kutsche, 1998). These narratives will be coded to highlight information relevant to the research questions. The resulting codes will be grouped into overarching themes (De Munck and Sobo, 1998). To minimize subjective bias, the coding process will again be performed by two independent researchers and reviewed by a third (Golafshani, 2003).

The qualitative component plays a central role in capturing the richness and complexity of human experience through embodied and art-based research approaches. Data will be analyzed using a multi-modal interpretative framework that integrates verbal narratives with non-verbal expressions such as images, bodily movements, and metaphorical representations. These diverse forms of data will be examined through thematic analysis, supported by visual and performative analysis techniques that allow for the identification of patterns, emotional resonances, and symbolic meanings. Embodied data analysis includes attending to bodily sensations, movements and gestures, often through somatic reflection, phenomenological interpretation and metaphorical mapping (Tantia, 2020). Art-based research allows us to explore ambiguity, emotion and complexity through creative modalities; artistic outputs are analyzed through visual narrative and thematic resonance (Gupta and Zieske, 2024). To enhance methodological rigor, triangulation will be employed across data sources and modalities, systematically comparing verbal accounts with embodied and artistic expressions to identify convergence, complimentary, and divergence in meaning-making (O’Cathain et al., 2010). This process will be supported by iterative coding strategies, cross-modal thematic mapping, and the development of integrative analytic matrices that bring together textual, visual, and embodied data (Fetters et al., 2013). The embodied and artistic outputs will be treated not merely as illustrative but as epistemologically significant, offering insights that transcend linguistic articulation and contribute to a deeper understanding of participants’ lived experiences (Fraser and al Sayah, 2011).

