### Sample size, recruitment strategy and inclusion criteria

2.2

The study aims to reach a total of 30 informal (i.e., relatives, friends, neighbors) and semi-formal caregivers (i.e., migrant family care assistant) and 15 older care receivers per country (total 90 caregivers and 45 older adults), without internal stratification considering the very low number of participants. The study is exploratory and is designed to generate in-depth insights into participants’ experiences rather than to test predefined hypotheses. Accordingly, no formal *a priori* power calculation was conducted, because the sample is intended to provide sufficient informational richness (i.e., “information power”) to address the research aims, rather than statistical representativeness. The sample size was decided upon because the few studies on the effects of dance-based interventions have included samples of this scale (Marmeleira et al., 2009), and others based on the use of multiple artistic mediums such as drawing and music involved approximately 20 subjects (McCarthy et al., 2019; Malyn et al., 2020). Furthermore, given that DanceCARE sample is representative for meaning and not statistically representative (Luborsky and Rubinstein, 1995), a study of the statistical power of the sample is not planned (Jones et al., 2003). Feasibility considerations, including recruitment capacity, available resources, and the intensity of the intervention, further informed the target sample size. To account for potential attrition, a dropout rate of approximately 10–15% has been anticipated, and recruitment will be adjusted accordingly where possible. Participant retention will be monitored throughout the study.

Informal and semi-formal caregivers are recruited using the snowballing method (Valerio et al., 2016), through word of mouth and by spreading leaflets in general practitioners’ ambulatories, geriatric hospitals, territorial health and social services, gyms, pharmacies, voluntary and caregivers’ associations, and through social media, i.e., Facebook and piloting organizations’ websites.

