Prior to the pilot phase, a small group of professionals—comprising two or three representatives from each country involved in the pilot project (hereinafter referred to as “mind–body trainers”)—will undergo specialized training, based on the aforementioned guidelines, on the intervention to be carried out with informal and semi-formal caregivers. All body–mind trainers have a background in DMT and are licensed through an institution recognized by the European Association of Dance Movement Therapy. All selected DMT trainers have on average over 5 years of work experience and are registered with national dance therapy associations.

Also, to ensure effective monitoring, each session will be attended by an observer—either a therapist specializing in DMT or a trainee selected at the national level through relevant associations and institutions. The observer will be provided with project guidelines, previously translated in the national language, for observing the body–mind sessions, thereby contributing to the collection of high-quality art-based and embodied material.

The intervention for the caregivers consists of 1 h and a half weekly face-to-face activities based on the DMT and WM techniques previously identified and developed in group for stimulating communication and peer networking, thereby counteracting isolation and the exacerbation of stress and other symptoms such as depression (Lauritzen et al., 2015). The frequency of the body–mind sessions has been defined during the construction phase of the programme through expert advice, but also through the collection of opinions of the caregivers themselves.

As shown in Figure 2, at each of the three pilot sites, 30 informal caregivers will be divided into three groups of up to ten participants, who will attend the program simultaneously on different days and at different times of the week for approximately 3 months, taking into account holidays and other factors that could slightly affect the timeline.

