The results that emerge are not to be considered exhaustive for caregiver’s emotional health status, that’s why the researchers decided to do an integration of measurements concerning specifically depressive aspects through BDI.

BDI is used as a screening tool for depression and to measure behavioral manifestations and severity of depression. Validity and reliability for BDI have been tested across populations, worldwide. It can be used from ages 13 to 80 and contains 21 self-report items which individuals complete using multiple choice response formats. The BDI score ranges from 0 (no symptoms of depression) to 63 (maximum depression). Scores above 40 already indicate extreme depression. Research indicates that a 17.5% change in the BDI score from baseline indicates a clinically significant change (Button et al., 2015).

Secondary quantitative outcomes are: the degree of satisfaction of caregivers with the intervention, assessed with ad-hoc closed and open questions; the quality of life perceived by the care takers, measured with a single question that can be answered with a score from 1 to 5, where 1 is “very good” and 5 is “very bad”; the care takers’ satisfaction with the care received, measured using a yes/no question and an open-ended question to provide explanations for their answer.

Considering the quantitative instruments, the screening questionnaire collects the socio-demographic data of the caregivers and information on the type and frequency of care provided, for the purpose of inclusion or non-inclusion in the study. It also includes questions about the willingness to attend the activities offered within the intervention and the expectations the caregivers have of it, in order to be able to adapt the activities as much as possible to the needs of the participants. The screening questionnaire evaluates the older person’s abilities to understand and answer the questionnaire by means of the Lawton Instrumental Activities of Daily Living (IADL) scale (Lawton and Brody, 1969) answered by the caregiver.

The questionnaire administered to caregivers before and after the intervention (at T0 and T2) contains the ZBI, the CBI and the BDI, as described above.

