### Study limitations, challenges and strengths

3.3

In this mixed-method study, bias can emerge from the quantitative component (e.g., randomization failures), the qualitative component (e.g., researcher subjectivity), or the integration of both. Common sources include selection bias (unrepresentative samples), measurement bias (inaccurate tools), and expectancy bias (researcher/participant preconceived notions). Given the meaning-based sampling procedure and the absence of a control group, we planned to mitigate potential biases by using various quantitative measures and combining them with qualitative data.

In particular, the proposed study presents some limitations and potential challenges that must be acknowledged. First, the recruitment process may prove demanding, as informal caregivers often face multiple constraints such as lack of time, physical exhaustion, emotional overload, transportation difficulties, and competing family responsibilities. These factors, combined with possible reluctance to participate due to privacy concerns or fear of being judged on their caregiving and/or movement abilities, may hinder enrolment. Furthermore, since recruitment largely depends on community networks and voluntary participation, there is a risk of selection bias toward caregivers who are already motivated or have more flexible schedules, which may limit the representativeness of the sample. Another challenge concerns participants’ adherence throughout the intervention. Given the vulnerability and daily burden of informal caregivers, dropouts may occur due to health deterioration, caregiving crises, or changing family circumstances.

Additionally, the small sample size and the pilot nature of the study limit the generalizability of the results. The qualitative data collection while providing deep insights may also be influenced by cultural and linguistic differences across the three participating countries, as well as by participants’ varying levels of comfort with embodied or art-based expression. Finally, although measures have been taken to standardize the protocol across pilot sites, differences in facilitation styles among DMT and WM trainers could introduce variability in intervention delivery.

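### Section 2.5 invokes intention-to-treat, but its rules give a completers analysis of the T0–T2 change: no method covers missing T2 outcomes

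*Protocol article*

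**What the plan says.** Four statements in the protocol article together fix how the effect on caregivers is analysed.

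- **Principle** (2.5 Data management and analysis): "In accordance with the intention-to-treat (ITT) principle, participants who withdraw from the study will not be replaced". No other consequence is drawn from ITT, and no analysis set is defined.
- **Missing data** (2.5): "Missing data in co-variates will be handled using multiple imputations via chained equations". Nothing is said about missing outcomes.
- **Test** (2.5): "Temporal comparisons (T0 vs. T2) will be conducted using paired-sample *t*-tests". Cohen's d for paired samples goes with it. Multivariate models are only considered if the univariate result is significant.
- **Measurement times** (2.4.1 Quantitative variables; Table 3 agrees): "The questionnaire administered to caregivers before and after the intervention (at T0 and T2) contains the ZBI, the CBI and the BDI". None of the three scales is scored at T1.

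Two further statements bear on how much this matters. Section 2.2 says that "a dropout rate of approximately 10–15% has been anticipated, and recruitment will be adjusted accordingly where possible". Section 3.3 warns that "dropouts may occur due to health deterioration, caregiving crises, or changing family circumstances".

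**The concern.** ITT is a rule about who is analysed. Not replacing people who leave is a rule about recruitment, and it does not keep anyone in the analysis. The article states the principle, the target of imputation and the test, and the three do not fit together. The one missing-data method applies to covariates, which do not enter a paired t-test at all. The values that dropout removes, the T2 scores, have no method.

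At stake is the pre–post change in ZBI, CBI and BDI and its effect size. These would be reported under a label implying that all enrolled caregivers are represented, while resting on those who returned the T2 questionnaire. Two of the three reasons for dropout named in section 3.3, worsening health and crises in caregiving, could well be linked to burden and depression. Those who return T2 may therefore differ in outcome from those who do not.

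**Working it through.** **Inputs from the article.** Target of 30 caregivers in each of 3 countries (2.2); dropout d of 10–15% (2.2); expected ZBI fall of at least 10 points at T2 (3.2 Expected outcomes); ZBI, CBI and BDI at T0 and T2 only (2.4.1).

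**Step 1: the plan's own figure.** 3 × 30 = 90 caregivers, which reproduces the stated total. There is no power calculation to reproduce.

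**Step 2: expected pairs, if drop-outs give no T2 data.** Pairs = 90 × (1 − d).
- d = 0.10: 90 × 0.90 = 81
- d = 0.15: 90 × 0.85 = 76.5

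So 9 to about 14 caregivers leave the effect analysis. The loss of precision is small. With an assumed SD of change of 15, the 95% half-width, t × SD/√n, is 3.14 points for n = 90, 3.32 for n = 81 and 3.43 for n = 76. The issue is who is represented.

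**Step 3: completers against all enrolled (illustration).** Mean improvement over all enrolled = (1 − d) × improvement in completers + d × improvement in drop-outs. Completers are set at 10 ZBI points. The drop-out values are assumptions, as the article gives none.

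| Assumed change in drop-outs | d = 0.10 | d = 0.15 |
|---|---|---|
| improve by 15 | 10.5 | 10.75 |
| improve by 10 (as completers) | 10.0 | 10.0 |
| no change | 9.0 | 8.5 |
| worsen by 5 | 8.5 | 7.75 |
| worsen by 10 | 8.0 | 7.0 |

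For example, with d = 0.15 and worsening by 5: 0.85 × 10 − 0.15 × 5 = 8.5 − 0.75 = 7.75.

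**Step 4: does the direction follow?** A simulation used a true mean change of −10. It assumed an SD of 15 at each time, a T0–T2 correlation of 0.5 or 0.7, and logistic dropout with slope 1 per SD at 10% or 15%. The completers-only change over those settings was:

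| Who drops out | Completers-only change |
|---|---|
| at random | −9.97 to −10.00 |
| those with worse T2 scores | −10.41 to −10.97 |
| those with higher T0 burden | −8.99 to −9.59 |
| those with better T2 scores | −8.99 to −9.59 |

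Benefit is overstated by up to about 1 point in the second row and understated by up to about 1 point in the last two. In the third row this happens because those with most room to regress towards the mean have left. The sign depends on a mechanism that the article does not state.

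**The case against.** The strongest reply is that little rests on this test. Feasibility is the main aim, retention and attrition are themselves reported outcomes, the study is exploratory and uncontrolled, and section 2.5 says that causal conclusions cannot be drawn. A condensed article also commonly leaves rules for missing outcomes to the full protocol. The first part stands and lowers the severity. The second does not remove the point, because the article makes a positive claim (ITT) that its own stated rules do not deliver.

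Four stronger readings are tempting, and the article does not support them.

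- **Every drop-out is lost.** Only caregivers without T2 scores are. Section 2.1 asks caregivers for the T2 questionnaire without limiting this to attenders, and section 2.4 says the scales go out as online forms. Someone who stops the sessions can still supply T2 data. The article does not say whether they will be asked.
- **The effect is inflated.** Section 3.3 says only that such dropout may occur, and its third reason, a change in family circumstances, has no obvious direction. Step 4 shows no bias under random dropout and a reversed bias under others.
- **A 10-point target would be wrongly declared met.** The 10 points in section 3.2 are an expectation, not a success rule, and section 2.2 says that no predefined hypotheses are tested. The outcome also depends on the assumed completer mean: at 12 points with drop-outs unchanged, the all-enrolled figure is 12 × 0.90 = 10.8 to 12 × 0.85 = 10.2.
- **The design promises 90 analysed caregivers and cannot deliver them.** At each site the 30 caregivers are "divided into three groups of up to ten participants", which leaves no spare places, but the article never promises 90 complete pairs. It aims to reach 90 and adjusts recruitment only where possible.

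It is also fair to say that a mixed model on T0 and T2, or imputation from T0, assumes missingness at random. Neither removes bias if people leave because they deteriorate after T0. That is why the fix includes a sensitivity analysis.

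**Conclusion.** The point holds as a mismatch between the ITT label and the analysis that section 2.5 specifies. As written, the T0–T2 result is a completers analysis, and no stated method covers missing T2 outcomes. At the anticipated dropout, and if drop-outs give no T2 data, about 76–81 of 90 caregivers contribute pairs. The estimate may be biased. A bias towards benefit is plausible from the reasons in section 3.3, but neither its direction nor its size is established. Over the drop-out changes assumed in step 3, the completers figure lies between 3.0 points above the all-enrolled improvement (10 against 7.0) and 0.75 below it (10 against 10.75). These are scenarios, not estimates. Severity is moderate.

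**What to change.** - **Label.** Call the paired t-test and paired Cohen's d completers analyses, or drop the ITT label. Define the analysis set in either case.
- **Main estimate.** Estimate the T0–T2 change in all caregivers with a T0 score. Use a linear mixed model with both scores as repeated outcomes, or extend the chained equations to the T2 ZBI, CBI and BDI with T0 scores, sessions attended, country and caregiver type as predictors. Given T0, this asks for missingness at random instead of completely at random.
- **Sensitivity.** Add an analysis with drop-outs set to no change and to a stated worsening, because the main estimate cannot cover dropout caused by later deterioration.
- **Data collection.** State that the online T2 form goes to every enrolled caregiver, whether or not they still attend.
- **Numbers.** State the expected 76–81 pairs, and reconcile the promise in 2.2 to adjust recruitment with the group capacity in 2.3 and the non-replacement rule in 2.5.

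The cost is changed wording, a little more programming and a possibly less favourable estimate.

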### Study design

2.1

The main aim of the study is to examine the feasibility of the innovative, blended, and flexible educational program based on DMT and WM methodologies. The second aim is to check if and how the application of key body–mind methodologies contribute to the reduction of burden, depression and isolation of informal and semi-formal caregivers, and at the same time to the increase of the quality of life of older care takers. The study wants to answer the following main research questions “Is the DanceCARE intervention feasible to implement in terms of recruitment, retention, adherence, and acceptability?” and “To what extent and how can the DanceCARE intervention change the perceived burden and depression levels of semi-formal and informal caregivers of older people with long-term care needs?”

Other research questions include whether the intervention also improves the quality of life of the older person receiving care, and whether the blended approach—which involves support through short online videos—is considered helpful and effective by the participants.

To answer these questions, this pilot convergent mixed-method study, chosen in preparation of a future full-scale study, integrates standardized quantitative instruments for measuring perceived levels of burden and depression, with diverse qualitative approaches to capture the complexity of human experience, e.g., interviews, focus-groups and live observations of participants during the body–mind sessions, enriched by art-based and embodied research approach (Hervey, 2000).

These qualitative data will not be limited to verbal accounts; they will also include symbolic and metaphorical expressions emerging from arts-based and embodied practices, which remain grounded within the qualitative paradigm and allow for a process-oriented understanding of participants’ experiences rather than capturing them at a single point in time.

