#### Quantitative variables

2.4.1

Feasibility will be evaluated using predefined indicators, including recruitment rate, retention and attrition, adherence to the intervention, and completeness of data collection. Acceptability will be assessed through participant feedback. These parameters will be summarized descriptively to inform the practicality and optimization of the study design.

Concerning the assessment of the impact of the intervention on participants, the primary outcome variables are caregivers’ burden measured using, respectively, the ZBI (Zarit et al., 1987, 1980; Chattat et al., 2011) and the CBI (Novak and Guest, 1989; Valer et al., 2015). The researchers further investigate the aspect of depressive state through the BDI (Beck et al., 1961). These are self-assessment, standardized psychometric instruments, in the form of questionnaires, which can be self-completed by the subjects. It was decided to use two tests to measure caregivers’ burden because the ZBI identifies the consequences of care-giving on the caregiver’s quality of life and psychological and social condition in general, while the CBI delves deeper into the dimensions related to specific individual areas of burden, i.e., objective, psychological, physical, social, and emotional burden.

The ZBI is the most widely used instrument. Originally designed and tested in 1980, it contains 22 questions. Its brevity allows for easy administration and requires the caregiver to respond via a 5-point Likert scale from 0 (never) to 4 (almost always) according to the degree of agreement they have with the individual items. The items investigate how the patient’s disability impacts the quality of life, psychological discomfort, guilt, financial difficulties, shame and social and family difficulties of the caregiver. Consequently, the total score, which is calculated by summing the individual item response scores, is between 0 which corresponds to no care burden, to a maximum of 88 which corresponds to a maximum level of care load. Values between 21 and 40 indicate a light to moderate care burden. Values between 41 and 60 indicate a moderate to severe care burden. Values between 61 and 88 indicate a severe care burden. Scores above 24–26 identify caregivers for whom further investigation and possible support interventions would be indicated (Schreiner et al., 2006).

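### A blanket p < 0.05 rule, with significance as the gate to further models, conflicts with a feasibility pilot that says it tests no hypotheses, so a change on one scale may be read as an effect

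*Protocol article*

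**What the plan says.** **Design and aim.** Section 2.1 states: "The main aim of the study is to examine the feasibility of the innovative, blended, and flexible educational program". Change in burden and depression is the second aim. Section 2.2 describes the study as exploratory, meant to give insight into experience "rather than to test predefined hypotheses", and reports that "no formal *a priori* power calculation was conducted". Section 2.5 repeats the priority: "Although the primary aim of the study is assessing the intervention feasibility".

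**Outcomes.** Section 2.4.1 lists the feasibility indicators first and says they will be summarised descriptively. It then turns to impact and says "the primary outcome variables are caregivers’ burden measured using, respectively, the ZBI" and the CBI. The BDI is added for depression. The two burden scales are not ranked.

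**Analysis.** Section 2.5 plans paired t-tests for T0 against T2, group comparisons by parametric or rank tests, chi-square tests and correlations. Significant univariate differences lead to consideration of multivariate models. The threshold is general: "A significance level of *p* < 0.05 will be used throughout". The same section promises effect sizes whether or not results are significant, and says that causal conclusions cannot be drawn.

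**Expectations.** Section 3.2 expects the ZBI to fall by at least 10 points, the CBI total by 10–20% and the BDI by 17.5%. It words a further expectation, on mood, as a hypothesis.

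**The concern.** A fixed significance threshold is a decision rule for hypotheses, and section 2.2 says the study has none to test. The rule also does some work in the plan: it decides what is modelled next. With two primary burden scales, no order between them and no label on the p-values, the plan does not say how to read a result in which one scale falls below 0.05 and the other does not. A report that led with the favourable scale would comply with the plan as written.

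Two different things can produce such a result without any benefit from the intervention. One is chance across several tests. The other is ordinary change over time in a study without a control group, whose caregivers enter only with raised self-rated stress. The abstract speaks of providing evidence of efficacy, and section 2.1 says the pilot prepares a full-scale study, so a misread result could shape that study.

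**Working it through.** **Inputs**

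- Threshold: 0.05 per test (section 2.5). Sidedness is not stated; two-sided is assumed.
- Scales with a T0–T2 comparison: ZBI total, CBI total and BDI (sections 2.4.1 and 3.2).
- Sample: "total 90 caregivers and 45 older adults" (section 2.2), with "a dropout rate of approximately 10–15% has been anticipated". Caregivers remaining if losses are not offset: 90 × 0.90 = 81; 90 × 0.85 = 76.5, taken as 77.
- Correlation between the scales' change scores: not given; 0.5 to 0.8 assumed.

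The article gives no power, overall error rate or derived sample size (90 is 3 × 30), so there is no figure of its own to reproduce.

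**Step 1. Chance of at least one p < 0.05 when nothing changes**

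For k independent tests the chance is 1 − 0.95^k. The correlated figures come from simulated paired t-tests with n = 77 and 40,000 runs.

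| Tests | Independent | Correlation 0.5 | Correlation 0.8 |
|---|---|---|---|
| ZBI, CBI (k = 2) | 1 − 0.9025 = 9.75% | 9.1% | 7.8% |
| ZBI, CBI, BDI (k = 3) | 1 − 0.8574 = 14.3% | 12.9% | 10.0% |

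At correlation 0 the simulation gave 9.65% and 14.0%, in line with the formula. These are two-sided rates, so they include chance worsening. Counting only chance improvement under independence, the figures are 1 − 0.975² = 4.9% and 1 − 0.975³ = 7.3%.

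**Step 2. Change over time that the intervention did not cause**

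With n = 77, a paired t-test is significant once the observed mean change reaches t(0.975; 76)/√77 ≈ 0.23 SD of the change scores. Suppose a non-causal drift of 0.2 SD (an assumption): one scale is then significant about 41% of the time. At 0.3 SD it is about 74%. A multiplicity correction is not aimed at this source of error, which can outweigh the figures in Step 1.

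**Step 3. The statements side by side**

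- Section 2.2: no predefined hypotheses and no power calculation. Section 2.5: one significance level for every test. Section 3.2: directional targets and a hypothesis.
- Sections 2.1 and 2.5: feasibility first. Section 2.4.1: primary is the word used for two burden scales, and not for the feasibility indicators.
- Section 2.5: no causal inference. The same section: significance decides whether further models are considered.

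**The case against.** Several points on the other side are sound.

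- **Primary is limited in scope.** Section 2.4.1 puts feasibility first and uses the word only for impact outcomes. The priority of aims is visible; what remains is a label to tidy.
- **The two scales have stated roles.** The ZBI covers general consequences for the caregiver and the CBI specific areas of burden. Preferring one as the single main measure is a choice, not a correction.
- **There are safeguards.** Effect sizes are reported regardless of significance, causal inference is disclaimed, section 3.2 states expectations by size, and section 3.3 acknowledges the missing control group and small sample. A reader might infer that a significant scale will be presented as an effect. The documents support only that it may be.
- **Unadjusted testing in an exploratory pilot is defensible.** A reader might infer that alpha must be split. Nothing in the design requires it.
- **A ranking of endpoints may sit in an unseen analysis plan.** Its absence from the article alone would not be a finding.

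A reader might also count many more tests. Adding the five CBI domains gives eight, and 1 − 0.95^8 = 33.7% (about 16–25% at correlations of 0.5–0.8). Twenty exposure comparisons would give 64.2%. The documents do not support these figures. Table 3 lists dimensions of burden against the CBI, but section 2.4.1 describes the domains as a graphical profile, section 3.2 refers to the CBI total, and no domain test is planned. The number of exposure comparisons is nowhere fixed.

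What survives is the conflict itself. The article, not an unseen document, fixes the blanket threshold and the gate, and the causal disclaimer neither labels a p-value as exploratory nor addresses chance.

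**Conclusion.** The point holds as a conflict between the stated testing rule and the stated design. The chance component is modest: 9.75% for the two primary burden scales (about 8–9% if correlated) and 14.3% with the BDI (about 10–13%). This assumes two-sided tests, one comparison per total score, and change-score correlations of 0.5–0.8 for the ranges. The exposure to uncontrolled pre–post change may be larger, but its size depends on a drift that the article does not give. Neither figure shows that the study will mislead. They show why significance is a poor basis for reading or steering this analysis, and why the wording is worth correcting before results are reported.

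**What to change.** - State that the feasibility indicators are the primary outcomes, and that changes in burden and depression are secondary and exploratory.
- Replace the blanket threshold in section 2.5 with the mean T0–T2 change and its 95% CI for ZBI total, CBI total and BDI, always reported together. The section now mentions 95% intervals only for odds ratios.
- Label every p-value exploratory, with no claim of significance for any scale.
- Remove significance as the trigger for multivariate models. If such models are wanted, choose them on other grounds.
- Reconcile sections 2.2, 2.4.1, 2.5 and 3.2, so that the targets in 3.2 read as benchmarks for interpretation and not as hypotheses under test.

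Naming one burden scale as the main effect measure is optional. No alpha correction is needed.

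The cost is wording only: no added participants, visits or data. The real price is that no result on any scale, the ZBI included, can be called significant.
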